### Recruitment and retention strategies

Women are reimbursed (by gift cards) for time spent completing surveys: $40 for the first portion of the baseline survey; $50 each for the second portion of the baseline survey, the 6 week postpartum survey, and both portions of the 6 month postpartum survey; and $70 for the 12 month postpartum survey. Checks for $40 are given for weight and blood pressure assessments at 6 and 12 months postpartum. No reimbursements are provided for participating in the intervention.

Of the 2,320 eligible women, 1,706 (73.5%) completed the baseline survey during pregnancy and 1,643 (70.8%) completed the survey at 6 weeks postpartum; 1,794 (77.3%) completed either the baseline survey or 6 weeks postpartum survey. There are no meaningful differences in the recruitment rates between treatment conditions (77.7% and 77.0%, respectively). Overall, responders and non-responders are very similar in regards to several characteristics, except that responders are slightly more likely to be Non-Hispanic White (20% vs. 26%) (Table 3).

**Table 3 T3:** Characteristics of survey responders and non-responders: the Gestational Diabetes Effects on Moms (GEM) study

	**All Sample**	**Non-responders**	**Responders**	**P-value**
	**N = 2,320**	**N = 526 (22.7%)**	**N = 1,794 (77.3%)**	
Age, years				0.21
18–24	119 (5.13)	33 (6.3)	86 (4.8)	
25–29	536 (23.1)	114 (21.7)	422 (23.5)	
30–34	863 (37.2)	184 (35.0)	679 (37.9)	
35–50	802 (34.6)	195 (37.1)	607 (33.8)	
Race/ethnicity				0.003
African American	106 (4.6)	28 (5.3)	78 (4.4)	
Asian	953 (41.1)	231 (43.9)	722 (40.3)	
Pacific Islander	38 (1.6)	13 (2.5)	25 (1.4)	
Hispanic	520 (22.4)	122 (23.2)	398 (22.2)	
Non-hispanic white	580 (25.0)	105 (20.0)	475 (26.5)	
Other	43 (1.9)	16 (3.0)	27 (1.5)	
Multiracial/Multiethnic	75 (3.2)	11 (2.1)	64 (3.6)	
Missing	5 (0.2)	0 (0.0)	5 (0.3)	
Parity				0.88
0	964 (41.6)	210 (39.9)	754 (42.0)	
1	769 (33.1)	158 (30.0)	611 (34.1)	
2	334 (14.4)	75 (14.3)	259 (14.4)	
≥3	208 (9.0)	46 (8.8)	162 (9.0)	
Unknown	45 (1.9)	37 (7.0)	8 (0.5)	
Pregravid BMI, kg/m^2^				0.11
<20.0	120 (5.2)	30 (5.7)	90 (5.0)	
20.0–24.9	667 (28.8)	163 (31.0)	504 (28.1)	
25.0–29.9	671 (28.9)	148 (28.1)	523 (29.2)	
30.0–34.9	417 (18.0)	76 (14.5)	341 (19.0)	
≥35.0	405 (17.5)	80 (15.2)	325 (18.1)	
Missing	40 (1.7)	29 (5.5)	11 (0.6)	
Gestational age at GDM diagnosis, weeks				0.75
5.6–13.9	286 (12.3)	61 (11.6)	225 (12.5)	
14.0–27.9	1092 (47.1)	245 (46.6)	847 (47.2)	
28.0–37.3	942 (40.6)	220 (41.8)	722 (40.3)	
100-g, 3-h OGTT glucose levels, mg/dl	*Mean (SD)*	*Mean (SD)*	*Mean (SD)*	
Fasting	91.3 (12.5)	90.4 (12.0)	91.6 (12.6)	0.05
1-hour	198.7 (25.2)	200.4 (25.0)	198.2 (25.3)	0.08
2-hour	176.9 (26.6)	178.1 (27.8)	176.5 (26.2)	0.24
3-hour	129.2 (32.9)	130.0 (34.1)	128.9 (32.5)	0.53
Systolic blood pressure, mmHg	114.3 (13.0)	114.1 (13.5)	114.3 (12.9)	0.69
Diastolic blood pressure, mmHg	68.1 (9.3)	68.0 (9.6)	68.1 (9.2)	0.90

GDM = gestational diabetes mellitus.

BMI = Body mass index.

OGTT = oral glucose tolerance test.

### Data safety and monitoring plan

This trial is monitored by an independent Data and Safety Monitoring Board (DSMB). The DSMB evaluates the progress of the trial with biannual assessments of participant recruitment, accrual and retention. We have restricted our EMR-based assessment of adverse events to those that could be related to the intervention (such as ankle sprains, etc.), or serious events that required hospitalization or a visit to the emergency department. For women who are no longer members of the health plan, adverse events are assessed via survey.

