### Pregnancy phase I

The target for the lifestyle program during pregnancy is to help women adhere to Institute of Medicine (IOM) guidelines for gestational weight gain [25]. Immediately following diagnosis with GDM, women are mailed a letter specifying a goal for total gestational weight gain by the end of pregnancy. The goal is tailored to women’s pregravid BMI and gestational weight gain trajectory (i.e., amount of weight gained relative to weeks of gestation). Since this population is at increased risk for having a larger than average infant and developing diabetes later in life, women who were normal weight (BMI 18.5-24.9 kg/m^2^), overweight (25.0-29.9 kg/m^2^), or obese (>30.0 kg/m^2^) before pregnancy are advised not to exceed the lower limit of IOM recommendations for their pregravid BMI (25, 15 and 11 lbs., respectively); women who were underweight (pregravid BMI < 18.5 kg/m^2^) are advised to gain at the midpoint of the IOM recommendations (34 lbs.) [25]. The letter explains that GDM increases diabetes risk, describes how weight management can aid in prevention, and provides healthy eating and physical activity tips to help women achieve their gestational weight gain goal.

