**Health & Medical Care**					
Perceived health	Survey	X	X	X	X
Pregnancy and postpartum care received	Survey		X		
Medical history	EMR/Survey	X	X		
Reproductive history	Survey	X			
Family history of diabetes and GDM	Survey	X			
Medication use	EMR/Survey	X	X	X	X
Gestational weight gain	EMR				
Infant feeding [33]	Survey		X	X	X
Medical visits	EMR/Survey				X
Health literacy [34]	Survey	X			
Use of contraceptives	Survey		X	X	X
Adverse events	EMR/Survey			X	X
Health status for cost evaluation [35]	Survey		X	X	X
Heath service utilization and cost	EMR/Survey		X	X	X

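### The intervention starts at GDM diagnosis, but Table 2 schedules adverse events only at 6 and 12 months postpartum and lists no infant outcome; neonatal losses are excluded with no split by arm.

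*Protocol article*

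**What the plan says.** **Start of the intervention** (Protocol article, Pregnancy phase I): "Immediately following diagnosis with GDM, women are mailed a letter specifying a goal for total gestational weight gain by the end of pregnancy". Women of normal weight, overweight or obese before pregnancy "are advised not to exceed the lower limit of IOM recommendations for their pregravid BMI"; underweight women "are advised to gain at the midpoint of the IOM recommendations". One reason the section gives for these goals is the raised risk of a larger than average infant.

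**Adverse-event schedule** (Table 2, Health & Medical Care): the row reads "Adverse events EMR/Survey X X". The pregnancy and 6-week columns are blank, and the two marks stand under 6 and 12 months. The 6-month window is defined as 12 to 34 weeks postpartum.

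**Adverse-event scope** (Data safety and monitoring plan): "We have restricted our EMR-based assessment of adverse events to those that could be related to the intervention (such as ankle sprains, etc", followed by "or serious events that required hospitalization or a visit to the emergency department". The DSMB is described as making "biannual assessments of participant recruitment, accrual and retention".

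**Other relevant items:** Table 2 lists gestational weight gain as an EMR item, without a time mark. Neither Table 2 nor the Outcomes section lists birth weight, gestational age at delivery or preterm birth. The eligibility section excludes 18 women for neonatal loss.

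**The concern.** The programme has a pregnancy component, and its adverse-event schedule begins after that component has ended. The protocol treats infant size as relevant to the weight-gain goal. It then names no measure of infant size, in the hoped-for direction or the opposite one. The most serious outcome that can follow the pregnancy phase, neonatal loss, is a ground for leaving the study population, although such a loss necessarily comes after diagnosis.

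The trial is meant to inform adoption by a health system, and individual consent for the intervention was waived. If the plan is followed as written, the final report could describe the safety of the whole programme without a by-arm account of pregnancy and birth.

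**Working it through.** **1. Timeline.**

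| Item | Place in the article | Timing |
|---|---|---|
| Weight-gain letter | Pregnancy phase I | at GDM diagnosis (5.6 to 37.3 weeks of gestation, Table 3) |
| First adverse-event mark | Table 2 | 6-month column, window opening at 12 weeks postpartum |

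If the windows bound what is captured (an assumption), nothing is scheduled from diagnosis to 12 weeks postpartum. The gap runs past the 6-week visit, because that column is blank too. With delivery assumed at 39 weeks, the pregnancy part lasts from 39 − 37.3 = 1.7 weeks to 39 − 5.6 = 33.4 weeks. The blanks do not look like an extraction fault: neighbouring rows carry marks in the pregnancy and 6-week columns.

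**2. What is and is not captured.**
- Too little maternal gain: measurable from the gestational weight gain item.
- Serious maternal events with hospital or emergency care: covered by the second class of events, whatever the cause.
- Infant size, preterm birth, neonatal loss by arm: no stated item. Nothing says that infants' records are searched, and a small or moderately preterm infant need not produce a maternal adverse event.

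**3. Neonatal loss.** 2,480 − 18 − 142 = 2,320, which reproduces the stated eligible number. 18 / 2,480 = 0.73%.

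**4. Exposure.** Table 3: (286 + 1,092) / 2,320 = 1,378 / 2,320 = 59.4% diagnosed before 28 weeks. This counts both arms. Only intervention-arm women received the goal, and no by-arm figure is given.

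**5. What a by-arm table could show.** Method: chi-square for two proportions, two-sided α = 0.05, power 0.80, design effect DE = 1 + (m − 1) × ICC, where m is the mean number of women per facility.

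Check against the protocol's own figures: with N = 2,320 and 70% followed, m = 2,320 × 0.70 / 44 = 36.9. The detectable difference is then 0.062 (base 0.15, ICC 0.01) to 0.107 (base 0.25, ICC 0.05). The article states 0.062 to 0.11, so the method reproduces it.

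Birth outcome: all 2,320 women, taken as 1,160 per arm, m = 2,320 / 44 = 52.7. The 10% base rate is an assumption. The ICC range is the protocol's 0.01 to 0.05.
- ICC 0.01: DE = 1 + 51.7 × 0.01 = 1.52; effective n = 1,160 / 1.52 ≈ 765 per arm; detectable rise about 4.7 points.
- ICC 0.05: DE = 1 + 51.7 × 0.05 = 3.59; effective n ≈ 323 per arm; detectable rise about 7.6 points.

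Base rates of 5% and 15% give 3.6 and 5.5 points at ICC 0.01, and 6.0 and 8.7 points at ICC 0.05.

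Unequal facilities: the Randomization section gives mean 57.5 and SD 50.3, so CV = 0.875 and CV² = 0.765. DE = 1 + ((1 + CV²) × m − 1) × ICC gives 1.92 and 5.60. At the 10% base rate the detectable rise becomes about 5.4 and 9.8 points.

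**The case against.** Several strong points can be made against this concern, and some of them stand.

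- A reader might infer that adverse events are limited to injuries. The text does not say so. The ankle sprain is an example within an open class of events that could relate to the intervention, and serious events form a second class.
- A reader might infer that harm from the pregnancy phase cannot be seen at all. That goes too far. Serious maternal events and gestational weight gain are available from the EMR. An extraction at 6 months could also look back to diagnosis. The gestational weight gain row has no time mark and is still plainly collected, so a blank cell does not prove non-collection.
- A reader might infer that the DSMB sees no safety data. One condensed sentence on trial progress does not show that; report contents may sit in a charter.
- The document does not itself name a small or preterm infant as a risk of the letter. Adding birth outcomes is partly a design judgement, and no primary or secondary analysis changes.

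These points narrow the concern but do not remove it. Table 2 is an explicit schedule that starts after the pregnancy phase. The protocol brings in infant size as a reason for the goal and then lists no infant outcome. The exclusion for neonatal loss is stated, not left unsaid.

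**Conclusion.** The concern holds in a limited form. The stated schedule does not match the stated start of the intervention. No stated item gives infant size, preterm birth or neonatal loss by arm. The known count at issue is 18 excluded women, 0.73% of 2,480, with the split unreported. How far back the 6-month adverse-event extraction reaches is unknown, so the length of any real gap is also unknown.

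The documents do not support a claim that harm occurred or that all harm is invisible. Nor do they support reading 59.4% as the share of women who carried the weight-gain goal early, since that figure pools both arms.

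Under the assumed 10% base rate, detectable rises of about 4.7 to 7.6 points (5.4 to 9.8 with unequal facilities) mean that a by-arm table would show only sizeable differences. It would describe safety and would not establish it. No view is taken on the weight-gain advice itself.

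**What to change.** 1. Reconcile the Pregnancy phase I section, the adverse-event row of Table 2 and the Data safety and monitoring plan by stating that the EMR adverse-event window starts at GDM diagnosis.
2. Add one by-arm table from the EMR: gestational weight gain relative to the guideline range, birth weight for gestational age, preterm birth, and neonatal loss among all 2,480 potentially eligible women by assigned facility.
3. Include the table in the DSMB report and the final report, labelled descriptive.

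The letter and its goals stay as they are. The cost is one EMR extraction and one table, with no new visits or contacts. The downside is a few extra comparisons with limited power, which the descriptive label addresses.

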### Evaluation of the intervention

To understand and inform the intervention’s implementation and potential for adoption by the health system [10] we conducted semi-structured interviews with KPNC clinical and operational leaders before the start of the study and at the end. At the end of the early postpartum phase, we will also conduct semi-structured interviews with the lifestyle coaches. Satisfaction with the intervention is assessed using a mailed questionnaire at approximately 8 months postpartum among women who completed at least one telephone session.

Data on direct medical costs of the intervention, which include all costs associated with implementing and maintaining the intervention (excluding the cost of evaluation), and all medical service costs, are collected through the EMR and surveys. In addition, at each survey, we ask participants if they were still KPNC members and if they have had any medical visits outside KPNC. We also assess perceived health status via survey with the EQ-5D [35].

### Statistical analyses, power and sample size considerations

All analyses comparing the effectiveness of each intervention strategy on our primary and secondary outcomes will be by intent-to-treat, including all eligible study subjects with measurements at all available time points, as appropriate to the outcome; analysis of treatment differences will be by original treatment condition assignment, regardless of adherence. The two primary outcomes for this study are the achievement of the postpartum weight goals and change in weight. Analyses will utilize marginal regression models for estimation of population average intervention effects, with linear mixed regression in analyses of weight change and logistic regression with estimation via generalized estimating equations (GEE) in analyses of reaching the weight goal. These regression models account for the within medical facility correlation between patients and within person correlation among repeated measurements, for valid estimation of treatment effects and associated standard errors. Variation in treatment group differences over time will be examined via the introduction of appropriate cross-product (interaction) terms between groups and time.

At the planning stage of this study, we expected a total sample size of 2,432 women diagnosed with GDM in a given year at the 44 facilities, and that approximately 76% would have weight measured at/near 12 months postpartum. Minimum detectable differences in the proportion meeting weight goals ranged from 0.060 to 0.10, across the range in expected proportion meeting goal in the usual care condition (0.15 - 0.25) and across the range in expected intraclass correlation (0.01 - 0.05) [chi-square test for two proportions, two-sided test, α = .05, power = .80]. For our actual sample size of 2,320 eligible women with GDM at the 44 facilities and with an expected 70% with weight measured at or near 12 months, the minimum detectable difference in proportions ranges from 0.062 to 0.11. The minimum detectable difference in mean weight at 12 months postpartum ranged from .16 to .23 standard deviation units at the planning stage, with no change in detectable effect sizes with the slightly lower actual sample size and proportion with weight measured at or near 12 months. These calculations are conservative, given that primary analyses will utilize multiple weight measures per person via mixed effects regression analyses.

The human subjects committee of the Kaiser Foundation Research Institute waived the requirement for individual informed consent for the intervention component, given the pragmatic, cluster randomized design [38,39]. For the survey component, women give verbal consent to participate via telephone. Women attending medical facilities randomized to the intervention can opt out of the lifestyle program at any time and individuals can also refuse participation in the study surveys or postpartum health check-ups at any time. All intervention and data assessment materials for the GEM study have been approved by the human subjects committee of the Kaiser Foundation Research Institute; the trial is also registered at clinicaltrials.gov (NCT01344278).

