**Psychosocial**					
Stage of change [21,22], Self-efficacy [20,23] and Social support [24]	Survey	X		X	
Perceived stress [36]	Survey	X		X	
Diabetes risk perception/knowledge [37]	Survey	X		X	

Weight, height, blood pressure, and blood glucose are measured in conjunction with routine care during pregnancy and throughout the 12-month postpartum period. Weight and blood pressure are measured at every health system encounter, since BMI and blood pressure are vital signs. Pregravid BMI is obtained from the EMR and calculated from weight measured prior to pregnancy (60.0%), from weight measured before 10 weeks of gestation (26.0%), from self-reported pregravid weight at the time of the first prenatal clinic visit before 10 weeks of gestation (10.5%), or self-reported at the baseline survey (3.5%). To determine the glucose tolerance status during the 12 months postpartum, the results of fasting glucose tests, 75-g oral glucose tolerance tests and hemoglobin A1c (glycated hemoglobin) are collected. All glucose and A1c tests are performed at the KPNC regional laboratory.

During pregnancy, the vast majority of KPNC patients with GDM (97%) have a clinic visit at their medical facility within 2 weeks of the diagnostic test for GDM, at which measurements of weight and blood pressure are taken. Postpartum clinical data are collected from the EMR at or near 6 weeks (range 2 to 11 weeks), 6 months (range 12 to 34 weeks) and 12 months (range 35 to 64 weeks); if a woman had multiple measurements of the outcome of interest in the range specified for a given time point, the value closest to the anchor (e.g., 6 weeks, 6 months and 12 months postpartum) is selected. KPNC patients with GDM receive a letter from the RPSC reminding them to attend a check-up at 6 weeks postpartum that includes measurements of weight, blood pressure and blood glucose. At 6 months and 12 months postpartum, the RPSC also sends a letter, for study purposes, reminding women to attend health check-ups for weight, blood pressure and blood glucose. Women also receive a telephone call reminding them to attend the postpartum health check-up. If a woman states that she is not able to attend the postpartum health check-up, she is asked to report her current weight.

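### The GEE for the weight goal needs a stronger missing-data assumption than the mixed model for weight change, and modelling correlation does not secure the validity the plan claims

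*Protocol article*

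**What the plan says.** The section on statistical analyses, power and sample size sets out an intent-to-treat comparison "including all eligible study subjects with measurements at all available time points". Of the two primary outcomes, reaching the postpartum weight goal is analysed by "logistic regression with estimation via generalized estimating equations (GEE) in analyses of reaching the weight goal", and weight change is analysed "with linear mixed regression in analyses of weight change". The models are said to account for correlation within facility and within woman "for valid estimation of treatment effects and associated standard errors". The working correlation for the GEE is not named.

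For the actual sample of 2,320 women the calculation goes on "with an expected 70% with weight measured at or near 12 months", which leaves 0.30 × 2,320 = 696 women without a 12-month goal status.

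The Outcomes section (text after Table 2) says that weights come from routine encounters and from check-ups prompted by letters and calls. There is a fallback: "If a woman states that she is not able to attend the postpartum health check-up", her current weight is requested by self-report. The ethics paragraph that closes the Methods lets women decline check-ups. Under Research goals, reaching the weight goal is the primary goal.

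**The concern.** Both primary outcomes are functions of the same weights, but the two estimators treat an absent weight differently. A likelihood-based mixed model uses a woman's earlier weights to account for selective absence later. If it is correctly specified, it is valid when missingness depends only on what was observed. An unweighted GEE has no such guarantee: it is assured of consistency only when, given the covariates in the model, missingness has nothing to do with the outcomes. Accounting for correlation serves standard errors and efficiency. It does not by itself make the estimated effect valid when weights are missing selectively.

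Weigh-in could plausibly depend on progress, and differently by arm, because intervention women are offered 13 coached sessions with self-monitoring of weight and usual-care women are not. If so, the goal-attainment difference could be biased even when earlier weights fully explain the missingness, and the two primary analyses could disagree for that reason alone.

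**Working it through.** **1. The plan's own figure.** Inputs from the statistical section: 2,320 women, 70% measured, 44 facilities, usual-care proportion 0.15 to 0.25, intraclass correlation 0.01 to 0.05, two-sided 5%, power 80%.

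- Analysed: 2,320 × 0.70 = 1,624. Per facility: 1,624 / 44 = 36.9.
- Design effect: 1 + 35.9 × 0.01 = 1.359, or 1 + 35.9 × 0.05 = 2.795.
- Effective number per arm: 812 / 1.359 = 597.5, or 812 / 2.795 = 290.5.
- Smallest detectable difference: 0.0624 (proportion 0.15, correlation 0.01). Largest: 0.1066 (0.25, 0.05).

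The plan states 0.062 to 0.11, so it is reproduced. Nothing below changes the sample size. The value 6.2 points serves only as a yardstick.

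**2. Illustration: assumed inputs.** There is no true effect, and 20% are at goal at both 6 and 12 months in both arms. The correlation between 6- and 12-month status is 0.6, and 70% are measured at 12 months. In the coached arm, being measured depends on 6-month status; in usual care it does not. Only the 20% (inside the planned 15% to 25%) and the 70% come from the article.

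- P(goal at 12 | goal at 6) = 0.2 + 0.6 × 0.8 = 0.68
- P(goal at 12 | not at 6) = 0.2 − 0.6 × 0.2 = 0.08

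**3. Independence working correlation.** The 12-month estimate is the proportion among women measured.

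- Measured 80% if at goal at 6 months, 67.5% if not: (0.2 × 0.80 × 0.68 + 0.8 × 0.675 × 0.08) / 0.70 = 0.217, or +1.7 points.
- Measured 90% and 65%: (0.2 × 0.90 × 0.68 + 0.8 × 0.65 × 0.08) / 0.70 = 0.234, or +3.4 points.

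These are 1.7 / 6.2 = 27% and 3.4 / 6.2 = 55% of the smallest detectable difference.

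**4. Per-woman exchangeable working correlation, same example.** With saturated visit means, the GEE gives, when the standard deviations at the two visits are about equal,

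estimate at 12 months ≈ M12 − a × (M6 − 0.20),

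where M12 and M6 are the 12- and 6-month proportions at goal among women measured at 12 months, and a is the estimated working correlation.

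- First case: M6 = 0.16 / 0.70 = 0.2286 and a ≈ 0.648, so 0.2171 − 0.648 × 0.0286 ≈ 0.199, or about −0.1 points.
- Second case: M6 = 0.18 / 0.70 = 0.2571 and a ≈ 0.694, so 0.2343 − 0.694 × 0.0571 ≈ 0.195, or about −0.5 points.

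With a = 0.6 the correction is exact: 0.2343 − 0.6 × 0.0571 = 0.200. It overshoots because selection raises the correlation among the women measured. If the scale parameter is held at one, the biases are −0.2 and −0.75 points. All are under 1 point.

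**5. When there is no bias in the difference.**

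- Weigh-in differing by arm alone: any constant rate k cancels, (0.2 × k × 0.68 + 0.8 × k × 0.08) / k = 0.20.
- The same selection in both arms under the null: both arms read 21.7% (or both 23.4%), so the difference is zero.

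**6. Wider check.** A large-sample simulation used three visits, correlation of the underlying weights within woman of 0.70 to 0.85, and about 30% missing at 12 months, with selection on the 6-month result in one arm.

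- Independence GEE: bias of +2.7 to +4.2 points.
- Per-woman exchangeable GEE: about 0 to +0.9 points.
- Linear mixed model: within 0.002 SD of the true mean difference.
- Same selection in both arms and a true difference of about 6 points: +0.1 to +0.7 points across the two GEE versions.

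A second simulation (44 facilities of 53 women, three visits, no true effect) added a GEE with a single exchangeable correlation per facility. Under 90%/65% selection the bias was +2.7 points (independence), +2.4 (per facility) and about 0 (per woman). Under 80%/67.5% it was +1.3, +1.0 and +0.1. Clustering on facility alone thus behaves almost like independence, because few pairs of records within a facility come from the same woman.

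**The case against.** The strongest reply is that the article says within-woman correlation is accounted for, and a GEE that does so per woman removes most of the bias. This stands as to size. It does not restore the guarantee: small bias remains in steps 4 and 6, and because no working structure is named, neither independence nor a facility-level structure is excluded.

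Second, a reader might infer that the GEE is valid only if weights are missing completely at random in the plain sense. That is too strong: missingness explained by arm or other modelled covariates does no harm, as step 5 shows.

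Third, a reader might infer that weigh-in will in fact favour successful women in the coached arm. The documents do not support this. They report no weigh-in rate by arm or by goal status. Reminders, payments and the self-report fallback are described without distinction by arm, and the fallback reduces missing weights. The similar rates of 77.7% and 77.0% concern surveys, so they settle nothing either way.

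Fourth, this is a condensed article, and weighting, imputation or sensitivity analyses may stand in an analysis plan that is not shown. That is right, and their absence here is not the point. The point is the primary method that the article does name and the validity it claims for it. GEE does suit a population-average target, and the remedy keeps it.

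**Conclusion.** The concern holds in a limited form. As stated, the primary analysis of goal attainment is guaranteed consistent only under a stronger missing-data condition than the co-primary analysis of weight change. Modelling correlation does not secure the validity claimed. With 30% of 12-month weights expected to be missing, this matters for the primary research goal.

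The size is conditional. With no true effect and selection on 6-month status in the coached arm only, the spurious difference in the worked example is +1.7 to +3.4 points under independence and less than 1 point in either direction under a per-woman exchangeable correlation. It would be wrong to read +1.7 to +3.4 as the expected bias of this trial: the selection pattern is assumed, and so is the working correlation. Nor is the mixed model a full safeguard. If weigh-in depends on the unseen current weight, neither it nor any other method that relies on missingness at random is protected.

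**What to change.** For the primary analysis of goal attainment, multiply impute the continuous weights separately by arm with a facility effect, using pregravid weight and all other observed weights. Derive goal status from the imputed weights and run the logistic GEE on the completed data. An inverse-probability-weighted GEE with the same predictors is an acceptable alternative. Keep the available-case GEE as a sensitivity analysis and name its working correlation. Reword the validity statement so that it gives the missing-data assumption behind each primary outcome.

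This needs no new data. The cost is a change of wording, modest programming, and reliance on an imputation or weighting model that must itself be reasonable. It brings the two primary outcomes onto the same assumption, but does not cover weigh-in that depends on the unseen weight.
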